## Abstract

**Background:**

One in three individuals who live in Rio de Janeiro experience a traumatic event within a period of 12 months. In the *favelas* particularly, trauma exposure is ongoing. Psychological sequalae include posttraumatic stress disorder (PTSD), depression and other mental disorders. Trauma-focused therapy approaches have emerged as the treatment of choice when the dangerous events are over, but symptoms have remained for an extended time period. Ideally, the victim is in a safe context during treatment. However, frequently, survivors cannot escape from situations characterised by ongoing threat and traumatic stress. The aim of this study is to research the effectiveness of Narrative Exposure Therapy in a sample of PTSD patients living under these conditions.

**Methods:**

Individuals fulfilling the criteria for PTSD and who live in conditions of ongoing community violence (i.e. in the *favelas*) in Rio de Janeiro will be randomly assigned to one of two treatments: Narrative Exposure Therapy (NET) or treatment as usual (TAU). Clinical endpoints will be primarily PTSD and secondarily symptoms of shutdown dissociation, depression, substance involvement  and functionality.

**Discussion:**

Effective treatment for PTSD patients who live in unsafe conditions could substantially reduce suffering of individuals and their families in Brazil. Based on this result, the extent to which such interventions may be useful as a first step in tackling the consequences of violence on a global scale will be discussed.

**Trial registration:**

Deutsches Register Klinischer Studien (German Clinical Trials Register) DRKS00017843. Registered on September 24, 2019

**Supplementary Information:**

The online version contains supplementary material available at 10.1186/s13063-021-05082-2.

## Introduction

### Background and rationale {6a}

About 114 million citizens of Brazil live in subnormal agglomerates (or *favelas*) [1]. These districts are characterised by social vulnerabilities such as lack of governmental services, poverty and high levels of violence [2]. About 35% of deaths by external causes in Brazil have been classified as homicides [3, 4]. In Rio de Janeiro particularly, the Western parts present with a high density of favelas. Here, the rate of homicides is about 10 times higher than in neighbourhoods of the South [5]. It is postulated that criminal organisations that are largely financed by trafficking of drugs and firearms play a major role in the escalation and the maintenance of high rates of violence [4]. The growing participation of children and youths is particularly alarming. The majority of individuals affected by urban violence are 25 years or younger [1]. According to a recent study by Ribeiro et al. [6], every third person in Rio de Janeiro had experienced a new traumatic event within 1 year. In the same sample, 87% reported at least one lifetime traumatic event [7]. Furthermore, insecurity and poverty affect familial relations and health [8]. In Brazil, the overall prevalence of intimate partner violence is estimated at about one third [9]. In a recent study, Serpeloni et al. [10] found that more than 50% of women who live in São Gonçalo city near Rio de Janeiro were exposed to intimate partner violence and 99% to community violence (e.g. witnessing fights, being threatened with a knife or a gun or witnessing killings). The risk of violence exposure remains high during pregnancy, a particularly sensitive period for mother and child. Common forms of violence are urban violence (60%), death of a close person (43%), accidents (34%), exposure to human remains (33%) or domestic violence (20%) [7]. About 71% of children reported hearing gunshots [7], 44% experience severe physical violence at home [11] and 22% of families experienced severe intimate partner physical violence [12]. In Brazilian women, mental health problems are particularly related to experiencing intimate partner violence [13]. Furthermore, family violence is a major determinant of mental health problems in children [12, 14]. Luz et al. [7] report an overall prevalence of 11% of posttraumatic stress disorder (PTSD) in Rio de Janeiro, assumedly with higher rates in low-income districts. Patients with PTSD have shown to be at a heightened risk for other mental disorders and also for experiencing more traumatic events. While subclinical tendencies of hypervigilance or avoidance may be adaptive at first, they substantially undermine the natural capacity to seek and avoid certain environments and intimate relationships. Evidence-based treatments for PTSD have been developed and tested [15]. Narrative Exposure Therapy (NET) [16] has emerged as an evidence-based treatment for patients in low- and middle-income countries and refugees, all of whom have been exposed to multiple traumatic stressors; for a review and meta-analysis, see Siehl et al. [17]. A substantial body of evidence shows the effectiveness of NET for patients who live in relatively safe conditions. Evidence is scarce however for circumstances of ongoing violence. Studies from post-conflict Eastern DR Congo with former combatants [18] and Iraqi women who live in a relationship with intimate partner violence [19] suggest beneficial but moderate effects so far.

Symptoms of posttraumatic stress are the result of intrinsic mnesic dynamics induced by the inherent properties of storing and retrieving information gathered during (multiple) traumatic events [20]. Fused neural fear associative networks of sensory, emotional, interoceptive and cognitive representations are separated from contextual and episodic memory systems [21]. Alarm responses can become activated by even small and subtle prompts. Re-experiencing occurs without the awareness of past and present. Intrusions, nightmares or flashbacks occur with a sense of the trauma happening again ‘here and now’. Trauma-focused therapy, in particular Narrative Exposure Therapy [16], is a specific form of psychotherapy for posttraumatic stress symptoms based on psychological theories of memory storage and retrieval [22]. During this treatment, the participant develops a narrative of traumatic events, which consolidates fragmented memories by connecting the associative representations with their respective context of time, place and situation (‘where’, ‘when’ and ‘what’). General trauma-related cues such as heart beating, sweating, fear, etc. are likely to occur in everyday life in a context of ongoing violence. Is it nevertheless possible to anchor the most traumatic events in the past and reduce symptom severity of PTSD? If so, is NET superior to treatment as usual and could improve care of trauma survivors?

### Objectives {7}

The aim of the study is to test the effectiveness of NET in a setting on ongoing violence in comparison to a treatment as usual (TAU) control group.

### Trial design {8}

The present study is a two-arm parallel group, observer-blinded, randomised, actively controlled clinical superiority trial with an allocation ratio of 1:1.

## Methods: participants, interventions and outcomes

### Study setting {9}

The trial is implemented in health centres in Rio de Janeiro (Brazil) in a joint project of the University of Konstanz and Claves/ENSP/Fiocruz. Collaborating health centres include Centro de Saúde Escola Germano Sinval Faria ENSP/Fiocruz, ENSP/Fiocruz (Manguinhos), Centro Municipal de Saúde Heitor Beltrão (Tijuca), potentially Clínica da Família Odaléa Firmo Dutra (Grajaú).

### Eligibility criteria {10}

Referred from the public health centres, individuals will be administered a baseline interview to be tested for eligibility. Eligibility criteria for participation in the trial are the following:
≥ 18 yearsDiagnosis of PTSD according to DSM-5Agreement to the written informed consent

Exclusion criteria:
Neuropsychiatric symptomsAcute psychotic symptoms (and/or under neuroleptic treatment)Other neurological disorder(s)

### Who will take informed consent? {26a}

Information about the trial is provided by the health centre and later in more detail at the beginning of the baseline interview that is conducted by trained local interviewers. Informed consents include a description of the study and the procedures and potential benefits and risk. The participants are also provided with an explanation about their right to discontinue participation at any point, that the treatment will be free and that there will not be a financial benefit besides the remuneration of transport to treatment and interview sessions. The informed consent can be found in Additional file 1.

### Additional consent provisions for collection and use of participant data and biological specimens {26b}

Not applicable as no biological data specimen will be collected.

## Interventions

### Explanation for the choice of comparators {6b}

In spite of the well-documented effectiveness of NET in general, there is a lack of evidence in comparison with symptom alleviating techniques provided in established health structures in a context of ongoing violence. Symptom alleviating techniques are commonly used to treat trauma-related symptoms when trauma-focused treatment cannot be applied due to the lack of stability of the patient (and his/her environment).

### Intervention description {11a}

#### NET counsellors

Trained Brazilian health personnel (medical/family doctors, psychologists) and advanced psychology students will deliver NET under constant supervision by a NET expert.

#### Narrative Exposure Therapy

NET will be delivered in 8–12 individual sessions of 90–120 min each in length by Brazilian NET therapists. The flexible number of sessions allows to test NET under naturalistic conditions and to adapt to the client’s trauma history. The initial session involves the construction of a lifeline whereby traumatic events are mapped out in chronological order and situated in the context of the patients’ lifetime period, as well as the wider systemic, and socio-political context at the time. A therapy plan is constructed according to the idiosyncratic experiences of the individual and traumatic events. In the subsequent exposure sessions, the most traumatic experiences are re-lived (emotional, sensory, cognitive, interoceptive) in order to transform the fragmented report of traumatic events into a coherent narrative. The therapist makes a written record of the event, and at the beginning of the next session, the narration is read to the patient and corrected for potential discrepancies. In the last session, the participant receives a written report of his/her biography.

#### Treatment as usual

TAU receives (or continues to receive) the services of our collaborating health centre (where they have also been recruited from). The treatment is not standardised and typically targets the symptoms reported by the patient (often diagnosed as hypertension, depression, panic disorder). TAU includes pharmacotherapy, empathic listening, problem solving and practical or social support [23]. It does not include deliberate trauma exposure which is a key characteristic of evidence-based trauma therapy. Treatment doses will be assessed retrospectively during follow-up assessments.

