### Outcomes {12}

Outcomes will be measured 3 and 6 months after the treatment. PTSD symptoms will be assessed as primary outcome using the PTSD Symptom Scale Interview for DSM-5 [24]. The Patient Health Questionnaire [25] will be used to measure depression severity. To assess trauma-related dissociation, we will use the Shutdown Dissociation Scale [26]. Substance involvement will be evaluation with the Alcohol, Smoking and Substance Involvement Screening Test [27]. Functionality will be assessed with the Work and Social Adjustment Scale [28]. Ongoing violence will be assessed by the scale Things I’ve seen and heard [29] and three questions asking whether the client has experienced any threat to physical or social integrity or was actively involved in violent perpetration.

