### Participant timeline {13}

An appointment for baseline assessment of trauma-related psychopathology will be scheduled by our study focal point with consenting individuals. Trained psychological interviewers will administer a structured, paper-based clinical interview (baseline, T0) to determine eligibility. Eligible patients will then be randomised and those allocated to the experimental condition will be contacted to start treatment at the next possible time point. Patients in the control condition will continue to benefit from the services of public health centres. Three and 6 months later, follow-up interviews (T1 and T2) will be conducted with the participants.

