## Assignment of interventions: blinding

### Who will be blinded {17a}

Trained master students in psychology will be blinded for the treatment condition of the participant, and they will conduct the baseline and follow-up interviews.

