## Data collection and management

### Plans for assessment and collection of outcomes {18a}

PTSD symptoms will be assessed using the PTSD Symptom Scale Interview for DSM-5 (PSS-I) [24]. The PSS-I-5 assesses for PTSD diagnosis according to the DSM-5 [34]. Scores for each item range from 0 (not at all) to 4 (≤ 6 times a week/severe). Diagnosis will be ascertained according to the manual, and sum scores were derived by adding all items of clusters B-E (max 80). Participants will be instructed to answer in relation to an index trauma (dominant in intrusions) with 1-month time frame. The Patient Health Questionnaire (PHQ-9); [25]) will be used to measure depression severity. The nine-item questionnaire is to be scored from 0 (not at all) to 3 (nearly every day) according to the presence of the symptom in the previous two weeks. A sum score will be calculated for depression severity (max 27). To assess trauma-related dissociation, we will use the Shutdown Dissociation Scale (ShutD) [26]. This 13-item questionnaire assesses sensory deafferentation (e.g. transitory deafness or blindness), reduced nociception/analgesia, numbness, transitory paralysis, loss of speech/suppressed vocalisation, pseudo-neurological symptoms, (pre-) syncopes and out-of-body experiences on a 4-point scale (0—not at all to 3—several times a week). All items were added to a total score ranging from 0 to 39. Good psychometric properties were found in previous studies [35]. The Alcohol, Smoking and Substance Involvement Screening Test (ASSIST) [27, 36] will be applied to assess the risk of drug consumption for alcohol, cannabis and other recreational drugs; risk scores (‘low’, ‘moderate’ and ‘high’) indicate the probability of drug dependence as well as social, financial, health and legal problems consequent to the drug abuse. The Functionality will be assessed with the Work and Social Adjustment Scale (WSAS) [28]. Ongoing violence will be assessed by the scale Things I have seen and heard [29] and three additional questions asking whether the client has experienced any threat to physical or social integrity or was actively involved in violent perpetration. The applied instruments have successfully been used in various cultures with good psychometric outcomes (see e.g. [37] for PSSI-5; [38] and [39] for PHQ-9; [26] for ShutD; [36] for ASSIST; [40] for WSAS; [29] for Things I have seen and heard). Trained interviewers administer the questionnaires under close supervision in their first interviews until interviewing techniques and rating meets high standards. If possible, interviewers will do sit in to ensure interrater reliability.

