## Oversight and monitoring

### Composition of the coordinating centre and trial steering committee {5d}

Fiocruz is responsible for the coordination of activities on site (e.g. arrangements with the health centres, ensure availability of rooms, etc.) and ensure study implementation follows the study protocol. Interviewer and NET trainings are led by AK and FS and supervision is conducted by FS, JN and AK. Fiocruz with the support of the University of Konstanz is responsible for data management, which encompasses all tasks concerning processing and utilisation of study data, with the aim of guaranteeing high-quality data and providing a valid study database for statistical analyses. The University of Konstanz (SC) will be responsible for conducting statistical analysis and the publishing of data.

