### Adverse event reporting and harms {22}

We expect a low frequency of SAEs caused by the NET itself. However, given the hostility of the environment, SAE will most likely be frequent. SAEs are events that (1) result in death, (2) are life-threatening, (3) require hospitalisation or cause prolongation of existing hospitalisation, (4) result in persistent or significant disability or incapability, (5) are a congenital anomaly or birth defect or (6) require intervention to prevent permanent impairment or damage (such as acute suicidality). SAEs will be monitored by the NET counsellors and interviewers. Together with their supervisor, they will decide which cases have to be followed up as SAEs and reported to the supervising clinical psychologist on site and the PI.

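### The stated follow-up and SAE procedures leave assessor blinding of the interviewer-rated primary outcome exposed, with no written safeguard

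*Protocol article*

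**What the plan says.** Trial design {8} describes a "two-arm parallel group, observer-blinded, randomised, actively controlled clinical superiority trial with an allocation ratio of 1:1". Section {17a} says who is blinded: "Trained master students in psychology will be blinded for the treatment condition of the participant, and they will conduct the baseline and follow-up interviews". Section {12} states that "PTSD symptoms will be assessed as primary outcome using the PTSD Symptom Scale Interview for DSM-5", and section {18a} treats it as a rated interview, with training until rating is satisfactory and attention to interrater reliability.

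On treatment received, the section Treatment as usual says "Treatment doses will be assessed retrospectively during follow-up assessments". The Participant timeline {13} describes no follow-up contact other than that "follow-up interviews (T1 and T2) will be conducted with the participants", at 3 and 6 months.

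On contact between the assessment and treatment teams, section {22} states: "SAEs will be monitored by the NET counsellors and interviewers. Together with their supervisor, they will decide which cases have to be followed up as" such events. Section {5d} begins "Interviewer and NET trainings are led by" and gives both trainings to the same people. It then names one supervision team without dividing it by role. Section {18a} adds: "Trained interviewers administer the questionnaires under close supervision in their first interviews". Section {17b}, on unblinding, is answered as not applicable because participants know their treatment.

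**The concern.** Participants cannot be blinded to NET, so the blinding of the interviewer is the main protection against biased rating of the PTSD interview. That protection is only as good as the procedures around it. If the person who rates PTSD severity also asks what treatment the patient received, or discusses a patient's SAE with the therapy team, the arm may become known. A rater who expects NET to work could then score NET patients lower without intending to. No later analysis can remove such a shift, and a larger sample does not reduce it. The observer-blinded label would then promise more than the trial delivers for its primary outcome.

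**Working it through.** No figure in the plan bears on this point, so the main check sets the sections side by side.

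1. **Who is at the follow-up visit?** Section {17a}: the blinded students conduct the follow-up interviews. Section {13}: these interviews, T1 and T2, are the only follow-up contacts described.
2. **What is collected there?** The primary and secondary outcome scales ({12}, {18a}) and, according to Treatment as usual, treatment doses. Steps 1 and 2 place dose collection in visits run by blinded raters.
3. **Could the dose question reveal the arm?** The sentence appears only under TAU. If only TAU patients are asked, being asked reveals the arm. If both arms are asked about all treatment, an account of 8–12 individual sessions of 90–120 minutes with a lifeline and a written biography identifies NET. If both arms are asked only about medication, the answer need not reveal anything, because section {11d} lets medication continue in both arms. TAU is broader than medication, however: it also covers empathic listening, problem solving and practical or social support.
4. **Does order settle it?** The order is not stated. Asking about doses after the PTSD rating would protect T1. It would not protect T2 if the same interviewer returns, and the article does not say whether that happens.
5. **SAE route.** Section {22} gives interviewers a part in deciding which cases are followed up, and it expects SAEs to be frequent in this setting. Section {11b} calls for examining a causal link with the intervention, which requires knowing the treatment.
6. **Safeguards stated.** There are none for assessors beyond the statement that they will be blinded. Section {17b} gives a reason that concerns participants only.

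**Sensitivity range (assumed bias, not from the documents).** Take a simple two-arm comparison of means at one time point, with n = 30 per group ({14}), two-sided alpha 0.05, no true effect, and a rating bias of b SD favouring NET. This is a normal approximation, not the planned mixed model.

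- Standard error in SD units: √(2/30) = 0.258.
- Shift: s = b / 0.258.
- Rejection rate: Φ(s − 1.96) + Φ(−s − 1.96).

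| Assumed b (SD) | s | Rejection rate (nominal 0.05) |
|---|---|---|
| 0.1 | 0.39 | 0.07 |
| 0.2 | 0.77 | 0.12 |
| 0.3 | 1.16 | 0.21 |
| 0.4 | 1.55 | 0.34 |

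The table shows what a bias of a given size would do. It does not show that any bias exists.

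**The case against.** A reader might infer that observer blinding breaks by design. The documents do not support that, for these reasons.

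- No section says that the blinded interviewer asks the dose question, that it comes before the PTSD interview, or that its wording discloses the arm.
- NET patients are referred from the same health centres and may stay on medication, so answers about centre contacts or drugs need not identify allocation.
- NET exposure is already documented through the therapists' written narrations and supervision records, so the follow-up interview need not ask about NET sessions.
- Shared trainers disclose no individual allocation. Section {5d} does not say whose supervision it means, and section {11c} describes NET supervision separately.
- The closely supervised first interviews are plausibly baseline interviews, held before randomisation ({16b}).
- In section {22}, the wording about their supervisor can mean each group with its own supervisor, and evaluation of SAEs rests with the on-site clinical psychologist and the PI ({11b}).

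A reader might also want a firm size, for example a share of the detectable effect. That is not available: section {14} gives no numeric d and refers to a within-group effect, and the documents give neither an expected bias nor an SD for the PTSD score.

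These points stand, and they remove the claim of a proven break. The shared-trainer argument adds little. It can further be said that an article leaves the order of forms and interviewer instructions to a fuller protocol. That answers only part of the point, because the exposure arises from procedures the article does state: doses at follow-up, follow-up run by blinded raters, and interviewers taking part in SAE decisions.

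**Conclusion.** The point holds as an exposure, not as a demonstrated failure. The sections on TAU, timeline and blinding put dose collection in the visits of the blinded raters. The SAE section gives those raters a task shared with the therapists, and the unblinding section does not consider assessors. This matters because the primary outcome is rated by interview and participants know their arm. The conclusion rests on one inference: that dose collection at follow-up assessments takes place within the T1 and T2 interviews, the only such contacts described. Whether unblinding would occur, how often, and how far it would move the PTSD score cannot be determined from the documents. The sections should be reconciled. The correction is cheap enough that it need not wait for evidence of harm.

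**What to change.** - **Treatment as usual and {17a}:** state that the PSS-I-5 and the other symptom scales are completed, scored and locked before any question about treatment received.
- **Who takes doses:** use someone who does not rate outcomes (existing non-assessor staff), or health-centre and NET session records. Alternatively, let interviewers ask only after the T2 ratings are locked. Either route keeps answers given at T1 from unblinding the T2 rating, which reordering the T1 form alone would not do.
- **{22}:** state that interviewers report possible SAEs but take no part in SAE decisions or NET supervision that reveal the arm. This concerns who sits in the discussion, not how an event is defined or managed.
- **Check on blinding:** have interviewers record a guess of the arm directly after the PSS-I-5, so that the blinding claim can be reported with evidence.

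**Cost:** a small change to the interview form and data flow. Dose data would come slightly later or from records. Using records assumes that they hold usable information on services received, which the article does not describe.
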